#### 4.4.3.2.3 About the ECG

a) ST-segment elevation myocardial infarction (STEMI): MI with ECG during index event showing persistent ST-segment elevation  $\geq 1$  mm in two or more contiguous leads ( $\geq 2$  mm if leads V2-V4) or new or presumably new LBBB.

b) Non-ST elevation myocardial infarction (NSTEMI): NI with ECG not showing either

of the two changes mentioned above.

c) Myocardial infarction with indeterminate ECG: Cases where the index event ECG is unavailable or was not performed.

#### 4.4.3.2.4. About the biomarkers peak

Biomarkers dosages (troponin or CKMB) will be requested from local labs, together with the normal reference values. The event adjudication committee's database will then store this data and the MIs will be classified according to the size estimated by the biomarkers peak in number of times of the ULN.

#### 4.4.3.5. Non-Ischemic Myocardial Injury

Cases that meet the criteria for biomarkers for MI, but where there is no evidence of ischemia based on ECG or imaging scans or symptoms will be classified as non-ischemic acute myocardial injury.

#### 4.4.3.6. Silent infarction

Defined as the appearance of a new Q wave or new area of non-viable myocardium on imaging scan (e.g.: echocardiogram) or anatomopathological finding of infarction, without a documented clinical condition or documented change in biomarkers.

### 4.4.4 Deaths (Mortality)

All deaths will be reviewed by the independent adjudication committee and the main cause leading to the fatal outcome will be determined. Source documents related to medical evolutions, test results, discharge summaries and death certificates will be requested from the sites when submitting the event.

#### 4.4.4.1. Cardiovascular (CV) Death

It includes death from coronary heart disease, sudden cardiac death, death from heart failure (HF), death from stroke, death from a CV procedure, death from CV hemorrhage, and death from other CV causes.

##### *I. Death from coronary heart disease*

Any death with a clear relationship to underlying coronary disease, such as death from myocardial infarction (MI), sudden cardiac death, and death as a complication of a coronary revascularization procedure.

Death caused by MI will be defined as death caused by a cardiovascular mechanism, as a direct consequence of MI (e.g., arrhythmia, cardiogenic shock, HF, mechanical complications, etc.), and occurring within 30 days of MI. Deaths caused by a procedure used to treat a heart attack (e.g.: coronary artery bypass graft surgery or coronary angioplasty) should also be considered as death due to MI. Sudden death cases preceded by a case positively adjudicated as IM will also count as deaths due to MI. This includes cases with MI discovered during necropsy, or when the diagnosis is made before the possibility of timely collection of markers (see definition of MI type 3 below).

##### *II. Sudden Cardiac Death*

It refers to unexpected death, not directly consequential to an MI, and includes the following possibilities:

- a) Witnessed death occurring without new symptoms or after worsening of old symptoms;
- b) Witnessed death, occurring within the first 60 minutes after the onset of new symptoms, unless the symptoms suggest an acute infarction (see definition of death from MI and definition of MI);
- c) Witnessed death, attributed to a documented arrhythmia (e.g.: in ECG tracing or while reading an implanted cardiac device, such as pacemakers and cardio defibrillators);

- d) Death within 30 days of failed CPR due to cardiac arrest of undetermined cause;
- e) Unexpected death, of unknown and unwitnessed cause in an individual known to be well in the previous 24 hours and with no clear signs that it may have been due to a non-cardiovascular cause (e.g.: trauma, poisoning. If the patient's status is not known in the 24 hours preceding the event, it should be considered as death of undetermined cause.

### *III. Death caused by heart failure (HF)*

It refers to death that occurs in the context of worsening HF signs/symptoms, such as cardiogenic shock, pulmonary edema or arrhythmias. If within 30 days of an MI, even if the MI caused the HF, it should be categorized as a death from MI.

### *IV. Death by Cerebrovascular Accident (CVA)*

It refers to death as a direct consequence of the stroke (e.g.: intracranial hypertension) or due to complications of stroke.

### *V. Death by CV procedure*

It refers to deaths as a direct consequence of complications from cardiac procedures, except those used to treat coronary heart disease or MI (at which time they will be classified as death from coronary heart disease or MI, respectively).

### *VI. Death due to cardiovascular hemorrhage*

Any death in the context of non-traumatic and non-procedural vascular rupture (e.g.: aortic aneurysm), hemorrhage causing tamponade (and not related to a CV procedure), and non-traumatic intracranial hemorrhage (excluding stroke cases).

### *VII. Death due to other CV causes*

It refers to deaths from CV diseases not included in the previous definitions (eg: pulmonary embolism, peripheral arterial disease).

#### 4.4.4.2. Non-cardiovascular death

It refers to deaths whose causes are not confirmed or suspected as cardiovascular. They may occur within the context of hospitalization for a CV event, but the cause of death does not involve a direct complication of the CV event (eg: a patient hospitalized for HF who dies from hospital pneumonia).

##### *I. Death from lung disease*

It refers to all death as a direct consequence of respiratory failure caused by a primary disease of the lung parenchyma, whether infectious or not. Excludes cases of death from pulmonary embolism or cardiogenic pulmonary edema (situations that will be considered as CV deaths).

#### **4.4.5 Hospitalization for Unstable Angina (UA)**

Hospitalization for UA will be defined as any unplanned hospitalization at the time of randomization due to an episode of precordial discomfort (or anginal equivalent), lasting  $\geq 10$  minutes, accompanied by at least one of the following characteristics:

Occurring at rest; OR

Occurring with decreasing levels of effort, in an accelerated pattern.

In addition, to meet the criteria for this event, there must be hospitalization within 24 hours of the last symptom, accompanied by at least one of the criteria below:

New or presumably new ST-segment or T-wave changes on resting ECG (in the absence of left ventricular hypertrophy or old LBBB), with at least 1 mm of transient ST-segment elevation, 0.05 mm of ST-segment depression or inversion of at least 0.3 mV of T-wave in leads with dominant R-wave;

Evidence of inducible ischemia in stress test performed in the same hospitalization (exercise test, bone scan, stress echocardiogram or magnetic resonance imaging);

Angiographic evidence of obstruction  $\geq 70\%$  or presence of thrombus as being responsible for the patient's symptoms;

Need for myocardial revascularization (PCI or CABG) in the same hospitalization or after subsequent transfer to another service without being discharged home.

#### **4.4.6 Hospitalization for Heart Failure (HF)**

Hospitalization for HF comprises all those situations where the patient is hospitalized for at least 24 hours with a primary diagnosis of HF and meets ALL of the following criteria:

a) The patient has at least one of the following symptoms of worsening HF: dyspnea, reduced exercise tolerance, fatigue, other symptoms of low cardiac output or volume overload (eg, ascites)

b) Objective evidence of signs of HF, through at least TWO signs on physical examination (edema; ascites; rales; hepatojugular reflux/increased jugular venous pressure; S3 gallop; rapid weight gain consistent with fluid retention) or ONE physical examination sign plus at least ONE laboratory or imaging evidence (increased atrial natriuretic peptides, radiological signs of pulmonary congestion, radiological or invasive evidence of increased filling pressures or low cardiac output)

c) The patient receives a new therapy or an increase in the previous therapy specifically for HF, such as:

- Increased dose of oral diuretic
- Intravenous use of diuretics, vasodilators or inotropic agents
- invasive therapy for HF, such as mechanical circulatory support or ultrafiltration.

If the primary cause of hospitalization is not HF, but HF is a factor that decisively contributes to the prolongation of a previous hospitalization, the event will also be positively adjudicated, provided it meets the criteria above (eg: HF complicating a hospitalization for MI).

#### **4.4.7 Hospitalization for respiratory infections**

Comprises all cases of hospitalization that have a primary diagnosis of respiratory tract infection, including tracheobronchitis, sinusitis, pneumonia, lung abscess or pleural effusion of a clearly infectious nature. The event must meet all of the following criteria:

- a) Hospital stay longer than 24 hours due to the diagnosis of infection;
- b) Evidence through imaging scan or clinical examination of involvement of the respiratory tract;
- c) Initiation of specific antimicrobial, antifungal or antiviral therapy.

Cases of exacerbated chronic obstructive pulmonary disease with respiratory infection as a contributing cause will also be considered, provided they meet the criteria above.

If the primary cause of hospitalization is not infection, but infection is a factor that decisively contributes to the prolongations of a previous hospitalization, the event will also be positively adjudicated, provided it meets the criteria above (eg: nosocomial pneumonia complicating a hospitalization for MI).

Hospitalizations for respiratory infections will be subdivided into upper airway infections (URTI) and lung infections.

##### ***4.4.7.1 Hospitalization for upper airway infection***

Comprises infections involving the ear, nose, throat, paranasal sinuses, larynx and trachea. Diagnosis can be made by evidence of clinical examination (eg: tympanic membrane bulging, posterior pharyngeal secretion, tonsil hyperemia).

##### ***4.4.7.2 Hospitalization for pulmonary infection***

Comprises infections involving bronchi, bronchioles, lung parenchyma and pleural cavities. For the diagnosis of this type of infection, a compatible imaging scan is necessary (eg: chest X-ray or CT).

#### 4.4.8 Myocardial revascularization due to ischemia

Comprises the need for myocardial revascularization (by CABG or PCI) due to findings compatible with ischemia, such as symptoms of angina (or anginal equivalent) or ischemia shown in non-invasive functional tests (eg, ergometric test) or invasive (such as fractional flow reserve – FFR). This definition includes all cases of revascularization due to an ischemic cardiac event (see items myocardial infarction and unstable angina).

The attempt to intervene in a lesion, even if unsuccessful, will be considered a revascularization event, if it meets the criteria above. In the case of percutaneous revascularization, the attempt to introduce a guidewire in order to implant any device aimed at unblocking the target vessel should be considered a revascularization event (including stent angioplasty, balloon angioplasty, atherectomy or thromboaspiration) . Isolated invasive diagnostic tests are not considered revascularization procedures, even if invasive physiology (such as FFR) or intracoronary imaging (such as intravascular ultrasound) are performed.

Myocardial revascularizations will be classified into urgent and non-urgent (elective):

*I. Urgent myocardial revascularization*

The procedure is required in a rapid period (eg, < 24 hours), usually due to an acute situation, when a delay in performing the procedure would entail a risk of deterioration in the patient's condition.

*II. Non-urgent revascularization*

The procedure is performed on an elective basis, usually in a stable condition, when the delay does not imply a risk of deterioration in the patient's clinical condition.

#### 4.4.9 Stent thrombosis

Stent thrombosis will be an event assessed through reports of angiographic procedures. There will be no analysis of the coronary angiography image by the adjudicators. Stent thrombosis will be defined as definite, probable or possible, according to the criteria of the Academic Research Consortium (ARC). All cases of stent thrombosis must have a corresponding clinical manifestation, namely, typical symptoms of ischemia at rest, ECG changes suggesting ischemia, OR elevation of biomarkers (see criteria for myocardial infarction). In addition, the thrombus must originate within the stent or in a segment 5 mm proximal or distal to the device. Stent thrombosis will fall into one of the following categories:

- A) Definite stent thrombosis: Angiographic evidence, by thromboaspiration specimen or by thrombus autopsy within a coronary stent mesh.
- B) Probable stent thrombosis: Myocardial infarction in a coronary territory compatible with a vessel submitted to previous stent implantation or unexplained death within 30 days after PCI with stent.
- C) Possible stent thrombosis: Unexplained death more than 30 days after PCI with stent.

#### 4.4.10 Safety endpoints

They will be monitored after the administration of the influenza vaccine for a period of 7 days following the occurrence of adverse events, which will be reported by face-to-face or telephone interviews by the HUB investigators and described in the CRF. AEs will be classified into two groups:

##### *(I) Local adverse events*

These will be described as reactions that may occur at the vaccine administration site, such as: erythema, edema, local pain, redness, limb or site induration and

ecchymosis. These reactions are benign, self-limited, and usually resolved within 48 hours. They will all be described, if they occur, in the CRF.

## **(II) Systemic adverse events**

These are benign and self-limited, such as fever, malaise, myalgia, hypersensitivity (anaphylactic) reactions and neurological manifestations (narcolepsy and Guillain-Barré syndrome, even without a cause-effect definition). These manifestations are more frequent in people who have not had previous contact with vaccine antigens.

Anaphylactic reactions (hypersensitivity type I) are extremely rare and can be related to any component of the vaccine. Some influenza vaccines may contain minimal amounts of egg protein, which may induce immediate allergic reactions in individuals with severe allergy to this protein. These events may be seen more frequently in individuals who have never had contact with the influenza vaccine. Fever will be classified into two groups by thermometer measurements: Fever condition will be classified when the mean body temperature presents values above 37.5 °C. Severe fever when the temperature is above 38.9 °C with or without hospitalization.

### **4.4.11 Seroconversion endpoint**

The humoral response to vaccination will be evaluated by the hemagglutination inhibition (HAI) test. In healthy individuals, HAI titers  $\geq 1:10$  indicate the presence of antibodies specific to the influenza virus, and titers  $\geq 1:40$  indicate protection from infection by the virus components in the tests, that is, the viruses that make up the vaccine. The following definitions will be used based on the results of the HAI tests: Titers  $<1:10$  = seronegative; Titers  $\geq 1:40$  or 4x baseline titers = protection against influenza. This 4x value will be used for assessment between the two intervention arms.

## **5. ADVERSE EVENTS**

An Adverse Event (AE) is defined as any untoward medical occurrence, including an exacerbation of a preexisting condition, in a clinical investigation patient who received a pharmaceutical product. The event does not necessarily have to be causally related to this treatment.

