### **SV2 - Safety evaluation after vaccine (28 /+ 3 days)**

-Evaluation of adverse events 28 days (+ 3 days) after the administration of double-dose vaccine (in person or by phone).

- **HOSPITAL DISCHARGE**

At discharge, describe:

- Clinical Evolution during hospitalization;
- Medications prescribed;
- Occurrence of endpoints.

- **V1 - 30 DAYS  $\pm$  5 DAYS FOLLOW-UP VISIT**

**Visit 30 days after randomization** This visit will be calculated from the date of randomization.

Patients randomized to the late standard dose of influenza vaccine will receive it at this visit.

At this visit, patients who were given double-dose vaccine will be evaluated regarding the clinical evolution, endpoints of interest to the study and adverse events:

- Clinical Evolution;
- Occurrence of endpoints.

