## 4.3 Exploratory endpoints

Occurrence of local and systemic adverse events at 7 and 28 days after vaccination. Occurrence of serious adverse events related to vaccination and serious adverse events within 12 months; Occurrence of the primary endpoint between treatment groups within 45 days of randomization; Vaccine antigen responses  $\geq 4$  times baseline by hemagglutination inhibition test.

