### **5.1 Serious adverse event (SAE)**

Results (defined above) that meet the criteria for a SAE will not be reported as a SAE, but as outcomes. A SAE is defined as any AE that results in death, is immediately life-threatening, results in persistent or significant deficiency/disability, requires or prolongates the patient's hospitalization, is a congenital anomaly/birth defect, or should be considered serious by any other reason if it is an important medical event when based on proper medical judgment that could jeopardize the patient and may require medical or surgical intervention to prevent one of the other outcomes listed in the definitions above.

The intensity of the AE should be judged based on the following:

- Mild: Awareness of signs or symptoms that are easily tolerated
- Moderate: Sufficient discomfort to cause interference with usual activity
- Severe: Disabling or causing inability to work or perform usual activities.

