### 3.3. Analysis populations

The following analysis populations will be defined for statistical analysis:

**Screened** – All patients screened for the study – having an acute coronary syndrome (ACS) during the hospitalization phase.

**Eligible but not randomized** – All screened patients who were eligible but not randomized due to the inclusion/exclusion criteria of the study.

**Intention to treat (ITT)** – All eligible patients who received a randomization number, and analyzed according to the group to which they were assigned, regardless of receiving the vaccine or not.

**Per Protocol (PP)** – All ITT patients who did not have major protocol violation. A protocol violation means a patient who was randomized but was not eligible (had not inclusion criteria or had at least one exclusion criterion); a patient who was treated with an immunization different from the one the patient was randomly assigned (e.g., intervention arm being

[figure not shown]

vaccinated after discharge). Patients vaccinated out of the window in the control arm due to the COVID-19 pandemic will still be included in the PP population, but a sensitivity analysis will be done excluding those patients as well (modified PP).

**Modified PP** –Due to the COVID-19 pandemic, some patients from the control group were not vaccinated within the expected study window or were vaccinated with a vaccine other than the study vaccination. Therefore, a modified PP population excluded these patients, as well as those ones that were not vaccinated at all (except for deaths occurred before vaccine could be administered)

**Safety** - All patients who received the vaccine. Patients who were vaccinated out of window or with vaccines other than study immunization (e.g., from an outpatient clinic) due to the COVID-19 pandemic were included in this analysis. Patients were analyzed according to the vaccination arm received, regardless of the randomized arm.

To avoid bias, if a patient had entered into study more than once, and in all these entries, this patient was considered eligible (i.e. met all inclusion/exclusion criteria), only the “first” enrollment will be maintained at the “Eligible patient population”, and the other(s) were excluded, due to duplicity.

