The primary efficacy analysis of the study comprises the ITT population. Safety analysis was made for the Safety population. Efficacy endpoints were performed in the PP and modified PP populations, and safety endpoints in the ITT population, as sensitivity analyses.

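### Adverse-event definition, visit text and main safety set all follow vaccination, and no start at randomisation is stated, so the 12-month comparison of non-endpoint serious events can lean against the double dose

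*Combined protocol and SAP*

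**What the plan says.** Protocol section 4.3 lists as exploratory endpoints "Occurrence of serious adverse events related to vaccination and serious adverse events within 12 months". It does not say when the 12 months begin. The synopsis sets follow-up at 12 months from inclusion.

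Protocol section 5 places an adverse event "in a clinical investigation patient who received a pharmaceutical product". Section 5.1 builds on this: "A SAE is defined as any AE that results in death" or meets one of the other seriousness criteria. The same section removes trial endpoints from the category; they "will not be reported as a SAE, but as outcomes". SAP 5.7 analyses those events by the efficacy methods.

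Protocol 3.5 and 3.5.2 give the double dose during the index hospitalisation and the control vaccine at V1, 30 ± 5 days after randomisation. In both arms the safety contacts fall 7 and 28 days after that arm's own vaccine. The V1 description reads "At this visit, patients who were given double-dose vaccine will be evaluated regarding the clinical evolution, endpoints of interest to the study" and then goes on to adverse events. There is no matching sentence for controls. The V2 and V3 descriptions list adverse events without naming an arm.

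SAP 3.3 defines the safety population as "All patients who received the vaccine", analysed by vaccine received. It adds "safety endpoints in the ITT population, as sensitivity analyses". SAP 5.1 reports the number and percent of unexpected serious events, without a time origin. SAP 5.2 specifies no between-arm test for serious events.

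**The concern.** The two arms are vaccinated about a month apart, early after an acute coronary syndrome. A safety clock tied to vaccination suits injection-site and systemic reactions. It does not suit a 12-month comparison of all serious events, because the arms then cover different stretches of the illness. The double-dose arm would carry non-endpoint serious events (for example bleeding, arrhythmia or renal events) from its hospital stay onward. The control arm would carry only those after about day 30.

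The vaccinated-only safety set adds a selection: a control must survive and stay in the study to V1 to enter it, while a double-dose patient enters in hospital. SAP 3.3 itself refers, under the modified per-protocol set, to patients not vaccinated at all.

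Both features push the same way. A reader of the 12-month table could take a later clock in controls for harm from the double dose. If the monitoring committee's comparative safety tables (Protocol 9.7) were built on the same set, they would share the problem. The documents do not say which serious-event tables the committee receives.

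**Working it through.** The plan gives no serious-event rate, so it has no figure to reproduce. The check is first structural, then an illustration.

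**1. The arms side by side**

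| Item | Double dose | Control |
|---|---|---|
| Vaccination (Protocol 3.5) | index hospitalisation | day 30 (25 to 35) |
| Discharge list (3.5.2) | clinical evolution, medication, endpoints | same |
| 7-day safety contact | 7 days after in-hospital dose | 30 + 7 = about day 37 |
| 28-day safety contact | 28 days after in-hospital dose | 30 + 28 = about day 58 |
| V1 text | adverse events named | adverse events not named |
| V2, V3 text | adverse events, no arm named | same |
| Main safety set (SAP 3.3) | entered in hospital | entered only if V1 vaccine is given |
| Endpoint events (Table 2, SAP 5.7) | from randomisation | from randomisation |

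The asymmetry is confined to serious events that are not endpoints, between in-hospital vaccination and the control vaccine.

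**2. Length of the window**

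Follow-up is taken as 365 days from randomisation.

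- Double dose on day 0: 365 days. On day 7 (assumed latest): 365 − 7 = 358 days.
- Control: 365 − 30 = 335 days (330 to 340 over the V1 window).
- Central ratio under a constant hazard: 365/335 = 1.09.
- Extremes: 358/340 = 1.05 and 365/330 = 1.11.

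**3. Front-loaded events (assumptions, not in the documents)**

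Suppose the true hazard is the same in both arms and, in the first 30 days, is k times the later hazard. Controls are counted from day 30 and double-dose patients from day 0. With a counted control risk of 10%:

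λ = −ln(1 − 0.10)/335

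Double-dose risk = 1 − exp[−λ(30k + 335)]

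| k | Double-dose risk | Spurious risk ratio | Chance of a false significant excess, 900 per arm |
|---|---|---|---|
| 1 | 10.85% | 1.085 | 8.5% |
| 3 | 12.51% | 1.251 | 39% |
| 5 | 14.15% | 1.415 | 77% |

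For counted control risks of 5% to 20%, the ratio is 1.23 to 1.26 at k = 3 and 1.38 to 1.43 at k = 5. The last column supposes a two-sided 5% test, which the SAP does not plan for serious events. The nominal chance in this direction is 2.5%.

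The model assumes no capture of early control events and full capture in the double-dose arm. Any early capture in controls moves the ratio towards 1. The effect of dropping unvaccinated controls is not included, because the documents do not give their number.

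**4. After the fix**

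Both arms are counted over 365 days, so the artefactual ratio is 1.00.

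**The case against.** A reader might infer that first-month serious events are not collected in controls, and that the 12-month comparison is therefore biased. The documents do not support that as a statement of fact.

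- The section 5 sentence defines a term and is not a collection rule. It refers to a pharmaceutical product in general, and controls receive drug treatment for their coronary syndrome from admission.
- The discharge list includes clinical evolution in both arms, so an event that prolonged the stay should be on record.
- The V1 sentence is loosely drafted. Read as excluding controls, it would exclude them from endpoint assessment too, which Table 2 contradicts. The clinical-events row of Table 2 is marked at the safety contacts, discharge and V1 alike, and may be meant to include adverse events.
- Protocol 5.4 requires the coordinating site to be told of any serious event, without limit by arm or vaccination. Section 4.3 separates vaccination-related serious events from those within 12 months, which suggests one clock from inclusion.
- Deaths, infarction, stroke, heart failure and the other endpoints are outside the problem.
- The endpoint is exploratory, no serious-event test is specified, and an intention-to-treat safety analysis is already planned.

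All of this stands as a limit on the claim. It does not remove the defect. Table 2 settles endpoint capture in controls, but no text settles adverse-event capture in the same way. The intention-to-treat analysis returns unvaccinated controls to the denominator but cannot restore events that were never recorded. The vaccinated-only set remains the main safety set by an explicit rule.

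**Conclusion.** The point holds for serious events that are not trial endpoints, and for the plan as written. Definition, V1 wording, control contact dates and main safety set all follow vaccination, and no passage sets a start at randomisation. The exploratory 12-month comparison can then give the double-dose arm about 30 extra early days and omit controls who die or leave before vaccination. Both effects lean against the double dose.

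The size cannot be derived from the documents. The window alone gives about 1.09 (1.05 to 1.11) under a constant hazard. The larger ratios rest on assumed front-loading and on no early capture in controls.

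Whether early control events were in fact missed is unknown. If sites recorded them from randomisation, one sentence settles collection and only the choice of main analysis set remains.

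**What to change.** In Protocol sections 4.3 and 5, state that serious adverse events count from randomisation in both arms, whether or not vaccine has been given. In 3.5.2, make the adverse-event review at discharge and V1 the same in both arms, with the V1 review of controls done before their vaccine. In SAP 3.3 and 5.2, make the main 12-month serious-event comparison an all-randomised analysis by assigned arm with time from randomisation, and move the vaccinated set to sensitivity. Keep the vaccinated set and the vaccination clock for local and systemic reactions at 7 and 28 days.

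The contacts already exist in both arms, so the prospective cost is a few questions and the amended wording. The real cost is retrospective. The last stated inclusion period ends in November 2021, so the latest scheduled V1 would fall by about 4 January 2022 (30 November + 35 days), before SAP version 2.0 of 14 March 2022. For patients past V1, in-hospital events can be taken from the discharge record. Events between discharge and V1 must come from readmission records or patient recall and may be incomplete. That should be reported as a limitation, with the source of early events given by arm.
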